## Abstract

**Background:**

Electroporation is a novel treatment technique utilizing electric pulses, traveling between two or more electrodes, to ablate targeted tissue. The first in human studies have proven the safety of IRE for the ablation of renal masses. However the efficacy of IRE through histopathological examination of an ablated renal tumour has not yet been studied. Before progressing to a long-term IRE follow-up study it is vital to have pathological confirmation of the efficacy of the technique. Furthermore, follow-up after IRE ablation requires a validated imaging modality. The primary objectives of this study are the safety and the efficacy of IRE ablation of renal masses. The secondary objectives are the efficacy of MRI and CEUS in the imaging of ablation result.

**Methods/Design:**

10 patients, age ≥ 18 years, presenting with a solid enhancing mass, who are candidates for radical nephrectomy will undergo IRE ablation 4 weeks prior to radical nephrectomy. MRI and CEUS imaging will be performed at baseline, one week and four weeks post IRE. After radical nephrectomy, pathological examination will be performed to evaluate IRE ablation success.

**Discussion:**

The only way to truly assess short-term (4 weeks) ablation success is by histopathology of a resection specimen. In our opinion this trial will provide essential knowledge on the safety and efficacy of IRE of renal masses, guiding future research of this promising ablative technique.

**Trial registration:**

Clinicaltrials.gov registration number NCT02298608.

Dutch Central Committee on Research Involving Human Subjects registration number NL44785.018.13

## Background

The past two decades have shown a steady increase in the incidence of small renal masses (SRM) up to 4 cm [1,2]. Nephron sparing surgery, in the form of partial nephrectomy, is considered to be the gold standard for treatment of SRMs [3]. Currently thermal focal therapies such as cryoablation and radiofrequency ablation (RFA) are primarily recommended in patients who are poor surgical candidates or have a genetic predisposition for developing multiple tumours [4-6]. However, promising long-term results combined with little or no loss in renal function have created interest in thermal focal therapies as a future treatment option for a broader range of patients [7-10].

Focal treatment of kidney tumour requires precisely dosed and accurate targeting of the tissue to be ablated while preserving surrounding healthy tissue and vital structures such as blood vessels, nerves, the renal collecting system and neighbouring organs [11]. The unselective destruction of currently practiced thermal ablation techniques can result in damage to vital structures in the vicinity of the tumour and undesired excessive ablation of normal parenchyma [12]. Thermal ablation intensity can be impaired due to ‘heat sink’ in the vicinity of large vessels and the renal collecting system [4].

Electroporation or electropermeabilisation is a technique in which electric pulses, traveling between two or more electrodes, are used to create ‘nanopores’ in the cell membrane. These pores allow for molecules to pass into the cell. The process can be temporary (reversible electroporation, RE), however above a certain threshold the ‘nanopores’ become permanent causing cell death due to the inability to maintain homeostasis (irreversible electroporation, IRE) [13-15]. It has been hypothesized that IRE is not dependent on temperature and is therefore not influenced by ‘heat sink’ promising consistent ablation results [11]. In theory IRE is defined to damage of the cell membrane, sparing tissue architecture and minimizing damage to blood vessels, nerves and the renal collecting system [16]. Recent literature however, has predicted [17] and measured [18,19] a large increase of temperature in healthy porcine kidney using currently practiced equipment and settings. As a result, it remains unclear to which extent the thermal effect or the electroporation contribute to the IRE ablation effect. Histopathology using viability staining of renal IRE lesions shows a sharp demarcation between ablated and non-ablated tissue allowing for precise targeting while sparing the surrounding healthy tissue [20,21].

Animal trials have assessed the use of MRI and CT imaging for the intermediate follow-up of IRE lesions. Contrast enhanced CT imaging directly after IRE ablation of porcine kidney showed a hypodense non-enhancing lesion, persisting at 1 week post IRE. At 3 weeks, 4 out of 6 IRE lesions had disappeared completely [22]. Thomson et al. performed in human IRE in 10 renal tumours with subsequent follow-up by CT imaging. At 3 months post IRE incomplete ablation was diagnosed in 2 patients on the basis of CT-imaging. However, the authors provide little information on the imaging characteristics of the residual lesion. MRI directly after IRE of porcine kidney showed a localized oedema at the region of IRE ablation. At 7 days after IRE a hypo-intense necrosis-like lesion in the renal parenchyma at the region of IRE was visualised. Finally, at 28 days a sharply delineated, non-intense, scar-like lesion with cortical shrinkage and without contrast enhancement was visualised [20]. These results provide an insight in the use of imaging for the follow-up of renal IRE. However, a study where follow-up imaging, specifically assessment of ablation volume and residual enhancing tumour, is correlated to histopathology of the resected specimen has not yet been performed.

Procedural safety of renal IRE in humans has been tested and confirmed [15]. The electric pulses administered during IRE have the potential of causing cardiac arrhythmias; by synchronising the IRE pulses with the ECG this complication can be avoided [23]. In a study by Pech et al., ablated tumours were resected directly after IRE and they observed swelling of cells but no actual cell death. However, histological staining to assess cell viability was not performed [15].

Before progressing to a long-term IRE follow-up study it is vital to have pathological confirmation of the efficacy of the technique. Furthermore, follow-up of IRE ablation requires an accurate imaging modality. This trial will investigate IRE ablation efficacy by correlating 3D histopathology of a resected IRE lesion with: 1) 3D reconstructed imaging using MRI and contrast enhance ultrasound (CEUS), and 2) the 3D predicted ablation volume as provided by the manufacturer. The objectives of the study are assessing the safety and efficacy of IRE of renal masses (primary objectives), and assessing the efficacy of MRI and CEUS for the initial evaluation and short-term (4 weeks) follow-up of IRE lesions (secondary objectives). This study conforms to the recommendations of the IDEAL Collaboration and can be categorised as a phase 2A development trial [24].

## Methods/Design

### Ethical consideration

The Institutional Review Board (IRB) of the Academic Medical Center, Amsterdam, approved this study protocol (2013_219). The protocol has been registered with The Dutch Central Committee on Research Involving Human Subjects (NL44785.018.13) and is entered in the clinicaltrials.gov database (NCT02298608). Potential candidates will receive the study information both verbally and in writing. They will be granted at least one week to decide on participation. Written informed consent is acquired from all participants.

### Study design

This is a prospective, human, in-vivo study among 10 patients presenting with a solid renal mass, and candidates for radical nephrectomy (RN). A study flowchart is provided in Figure 1. Prior to the IRE procedure baseline MRI and CEUS imaging will be acquired. Subsequently the patients will undergo IRE ablation of their renal mass. Follow-up at one and four weeks post IRE will be performed using MRI and CEUS imaging. At these time points procedure and device related adverse events (AE) will be registered using the Common Terminology Criteria for Adverse Events (CTCAE) version 4.0 guideline. Four weeks after IRE the patients will undergo radical nephrectomy after which pathological examination will be performed to evaluate IRE ablation success. Core biopsies are harvested before IRE ablation in order to assure tumour differentiation in case of complete ablation. Correlation between pathology and imaging will reveal the efficacy of MRI and CEUS for the assessment of IRE lesions.

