**Study design flowchart.**

### Study objectives

Primary objectives:To determine the efficacy of IRE ablation of renal masses, measured by pathological examination of the targeted tumour.To determine the safety of IRE ablation of renal masses, by evaluating device and procedural adverse events using CTCAE v4.0.

Secondary objectives:To evaluate the efficacy of MRI in the imaging of ablation success, the extent of the ablation zone, one and four weeks post IRE ablation.To evaluate the efficacy of CEUS in the imaging of ablation success, the extent of the ablation zone, one and four weeks post IRE ablation.

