#### Study procedures

##### Core biopsy (standard treatment)

Percutaneous renal core biopsy will be performed directly before the IRE procedure, utilizing the procedural anaesthesia. A minimum of two percutaneous core biopsies will be harvested for pathological examination. In the Academic Medical Center Amsterdam all patients presented with a renal mass on cross-sectional imaging, suspicious for malignancy, are advised to undergo renal core biopsies.

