##### CEUS and MRI imaging (study intervention)

CEUS and MRI imaging will take place at baseline, one week and four weeks after IRE ablation in order to assess lesion size and enhancement. Furthermore, this will reveal possible complications and any unexpected abnormalities as a result of the IRE procedure that may affect the final surgery (radical nephrectomy).

Contrast enhanced ultrasound (CEUS) utilizes a contrast agent to increase echogenicity of blood for better visualisation tissue vascularisation. Ultrasound contrast contains 3–5 μm microbubbles surrounded by a phospholipid shell. Early studies have shown promising results for the use of CEUS in the follow-up after cryoablation [26]. This study uses a Philips iU22 (Philips Healthcare, Bothell, USA) ultrasound device which is optimised for contrast studies, in combination with SonoVue (Bracco, Milan, Italy) a third generation ultrasound contrast agent with a elimination half-life of 6 min [27].

MRI will be performed using a Siemens Avanto 1.5 Tesla MRI scanner (Siemens Healthcare, Erlangen, Germany) with a 16-channel body array coil. The MRI protocol will include at least the following sequences: T2-trufi with fat suppression, T1-fl2d contrast enhanced in and out of phase, T2-haste, T1 vibe unenhanced and dynamic series at 30 seconds, 60 seconds, and 15 minutes. As MRI contrast agent Gadovist 1.0 (Bayer Pharma, Leverkusen, Germany) will be used.

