#### Potential benefits and risks

There are no benefits for patients that participate in this study. Study participants will be exposed to additional risk when compared to standard treatment. They will have to undergo an additional procedure under general anaesthesia with muscle relaxation. An independent expert, assigned by the IRB, has estimated the exposure to ionizing radiation during the IRE procedure at 32 mSv.

IRE is a new tissue ablation technology and IRE of renal tumours has only been tested in a limited number of patients. It might be that certain risks and side effects are unforeseen at this point in time. Potential risks associated with IRE for renal tumours, using the NanoKnife™ system, are listed in Table 2. In addition, it is not expected that renal IRE in patients with ERDS will result in an acute dependence on dialysis. Both animal and human studies did not show a substantial decrease in GFR following renal IRE ablation. Research among patients suffering from renal insufficiency has however not yet been conducted. Therefore the possibility of a decrease in renal function leading to the need for dialysis cannot be completely excluded.

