**Table 2 Tab2:** **Potential risks associated with IRE of renal tumours**

Potential hazards of renal IRE ablation	Potential effects
Excessive energy delivery	Muscle contraction, burn, damage to critical anatomical structure, unintended tissue ablated, bradycardia/hypotension, vagal stimulation/asystole, electrical shock, myocardial infarction, stroke, death
Insufficient/no energy delivery	Ineffective ablation, no ablation
Unintended mains or patient circuit voltage exposure to patient or user	Electrical shock
Incorrect timing of pulse delivery	Transient arrhythmia, prolonged arrhythmia, stroke, death
Unintended interference with implanted devices containing electronics or metal parts	Myocardial infarction, stroke, death
Unexpected movement of the device and displacement of the electrodes	Hypotension, damage to critical anatomical structure, pneumothorax, mechanical perforation, haemorrhage, unintended tissue ablated, electrical shock, death
Sterile barrier breach	Infection, sepsis

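### The primary safety outcome admits only adverse events already judged related, registered at one and four weeks, with no stated registration at or after nephrectomy

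*Protocol article*

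**What the plan says.** The Study objectives section of the Protocol article makes safety one of two primary objectives: "To determine the safety of IRE ablation of renal masses, by evaluating device and procedural adverse events using CTCAE v4.0". The Study design section sets the visits, "Follow-up at one and four weeks post IRE will be performed using MRI and CEUS imaging", and then the safety data collection: "At these time points procedure and device related adverse events (AE) will be registered". The nephrectomy comes next: "Four weeks after IRE the patients will undergo radical nephrectomy after which pathological examination will be performed to evaluate IRE ablation success". No further time point for adverse events is given.

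Four other places bear on this:

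- **Core biopsy** (headed as standard treatment): "Percutaneous renal core biopsy will be performed directly before the IRE procedure, utilizing the procedural anaesthesia". At least two cores are taken.
- **CEUS and MRI imaging:** the scans are also meant to show complications and "any unexpected abnormalities as a result of the IRE procedure that may affect the final surgery (radical nephrectomy").
- **Potential benefits and risks:** the authors accept that some side effects may not yet be known. They add that, in patients with renal insufficiency, "the possibility of a decrease in renal function leading to the need for dialysis cannot be completely excluded".
- **Table 2:** the hazards include haemorrhage and, for mistimed pulses, "Transient arrhythmia, prolonged arrhythmia, stroke, death".

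**The concern.** Two features of the stated rule weaken a primary outcome.

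First, relatedness is a condition for entry. An event that the investigator does not attribute to the device or procedure need not enter the data, and later readers could not revisit that decision. This fits poorly with a technique whose risks the authors call incompletely known, because an effect nobody expects is easily put down to the underlying disease or to other care.

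Second, the stated registration points stop before the operation. If IRE alters the tissue in a way that makes the nephrectomy or recovery harder, no stated safety time point would pick that up.

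At stake is whether the safety result shows what happened to the 10 patients, or only what was attributed to IRE by the four-week visit.

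**Working it through.** The plan states no safety rate, threshold or interval, so there is no figure to reproduce. The check is mainly a comparison of sections.

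**1. Is the restriction a rule or an omission?** It is a rule. The limit to device and procedural events appears under both Study objectives and Study design, and the time points are named.

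**2. Does the four-week registration include the nephrectomy?** Not as written. The four-week visit is an imaging visit of the ablated kidney, so it must come before that kidney is removed. Pathology of the specimen (Analysis section) covers damage to vessels, collecting system and renal pelvis. It does not cover operative difficulty, blood loss or post-operative events.

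**3. Is the ablation session covered?** By definition, yes: an arrhythmia during pulsing is a procedural event. By observation, also yes. The IRE ablation section provides ECG monitoring under anaesthetic supervision, discharge at 24 hours if fit, and pain assessment at 4 hours, 24 hours and 1 week. What is not stated is that adverse events are recorded as they occur. The article gives early times for pain but none for adverse events.

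**4. Can attribution be made reliably?** Biopsy and IRE share one session and one anaesthetic. Haemorrhage is a Table 2 hazard and could equally follow a biopsy. Biopsy is labelled standard treatment and IRE the study intervention, so it is unclear whether a biopsy bleed counts as procedure-related. There is no control arm and the article gives no attribution rule.

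**5. How much does one event matter with n = 10?** Exact (Clopper-Pearson) 95% limits:

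- 0/10: lower 0; upper 1 − 0.025^(1/10) = 0.308, so 0–30.8%.
- 1/10: lower = 2.5% point of Beta(1, 10) = 0.0025; upper = 97.5% point of Beta(2, 9) = 0.445, so 0.25–44.5%.

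One patient is 1/10 = 10 percentage points. The chance of at least one event, 1 − (1 − p)^10, for assumed true rates p:

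| Assumed p | P(at least one event in 10) |
|---|---|
| 5% | 40% |
| 10% | 65% |
| 20% | 89% |
| 30% | 97% |

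An event type with a true rate of 5–10% may well occur only once or not at all, so whether a single event is recorded matters.

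**The case against.** The strongest reply is that the registration sentence says when events are entered, not which moments count. On that reading, events during ablation are covered and a bleed after the combined session can be entered as procedural. The rest (start and end of the window, recording as events occur, handling of unrelated events) would sit in the full protocol, the DSMB charter or the study flowchart, none of which is shown. No safety rate or interval is planned, and the Sample size section says the numbers do not support reliable statistical analysis.

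Much of this stands, and it rules out several stronger readings that a reader might infer:

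- **That peri-procedural events are missed, or captured only by recall a week later.** They are within the definition and are observed. The article mentions no recall.
- **That nephrectomy is where IRE harm is most likely.** No section ranks periods by risk. The surgical concern under Population and in the Discussion is about partial nephrectomy. The imaging section supports only a possible effect on the radical operation.
- **That the reported rate is necessarily biased downward.** A biopsy bleed could equally be charged to IRE, and a difficult nephrectomy cannot be assigned to IRE without controls.
- **That the upper limit would rise from 31% to 56%.** That needs two hypothetical missed patients (2/10: 2.5–55.6%).
- **That omitting a renal function table is an error.** An article may leave this to the full protocol.

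The reply does not remove the core. The relatedness filter and the two time points are stated. A fuller document might add to them, but the published wording still narrows a primary outcome.

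**Conclusion.** The point holds in a limited form. As written, the primary safety outcome depends on an attribution judgement made before recording, in 10 uncontrolled patients whose biopsy and IRE share a session. It also has no stated registration at or after the nephrectomy, despite the expectation that IRE may affect that surgery. Relevant events can be lost; the documents do not show that they will be, or in which direction the net error runs. The absence of a statement on recording events as they occur is a matter for clarification.

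The size cannot be estimated from the documents. The only firm scale is 10 percentage points per patient, with the wide limits shown above. The conclusion assumes that the registration sentence is the operative rule and that no unseen document widens it. It is worth correcting because the change is cheap and the outcome is primary.

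**What to change.** Replace the registration sentence with a rule along these lines:

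- Register **all** adverse events by CTCAE v4.0 from the start of the biopsy/IRE session, through discharge, the one- and four-week visits, the nephrectomy and its routine post-operative recovery.
- Record relatedness as an attribute of each event (IRE, biopsy, nephrectomy, other or indeterminate), not as a condition for entry.
- Report all events and related events side by side.
- Show bleeding after the combined biopsy and IRE session in the primary safety table, with its attribution.
- Take intra-operative findings at nephrectomy descriptively from the operation note, without claiming that IRE caused them.

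If the full protocol already does this, the wording should be brought into line with it.

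The cost is a wording and case report form change plus slightly more data entry, drawing on anaesthetic, ward and operation records that should exist from routine care. The event count may look less favourable and will include events caused by the nephrectomy itself, which is why the attribution column and the side-by-side presentation are needed.

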**Figure 1 Fig1:**
[figure not shown]
**Study design flowchart.**

### Study objectives

Primary objectives:To determine the efficacy of IRE ablation of renal masses, measured by pathological examination of the targeted tumour.To determine the safety of IRE ablation of renal masses, by evaluating device and procedural adverse events using CTCAE v4.0.

Secondary objectives:To evaluate the efficacy of MRI in the imaging of ablation success, the extent of the ablation zone, one and four weeks post IRE ablation.To evaluate the efficacy of CEUS in the imaging of ablation success, the extent of the ablation zone, one and four weeks post IRE ablation.

#### Population

Ten patients with a solid enhancing renal mass and scheduled for a radical nephrectomy will be enrolled in this study. Eligible patients are over 18 years of age, and candidate for radical nephrectomy due to tumour size/stage, or ESRD (stage 4 or 5), or the need for a pre-emptive transplant kidney. The development of IRE is aimed at the ablation of small renal masses (SRM). According to EAU and Dutch Association of Urology (NVU) protocol the preferred treatment of a SRM in an otherwise functioning kidney is partial nephrectomy (PN). Performing IRE ablation in these cases might, however complicate a subsequent partial nephrectomy leading to impaired surgical outcomes. Therefore we will strictly include patients with a renal mass who are planned for radical nephrectomy. All inclusions will be reviewed for safety and eligibility by a nephrologist participating in the research project. The inclusion and exclusion criteria for this study are listed in Table 1.

**Table 1 Tab1:** **Inclusion and exclusion criteria**

Inclusion criteria	Exclusion criteria
○ Age ≥ 18 years	○ Irreversible bleeding disorders
○ Solid enhancing mass on cross sectional imaging	○ Inability to stop anticoagulation therapy
○ Scheduled for open or laparoscopic RN	○ Prev. cryoablation, RFA or PN affected kidney
○ Signed informed consent	○ Anaesthesia Surgical Assignment (ASA) cat. ≤ IV
	○ ICD or pacemaker
	○ Severe cardiovascular disease

Severe cardiovascular disease is defined as the diagnosis of myocardial infarction, uncontrolled angina, significant ventricular arrhythmias, stroke or severe cardiac failure (NYHA class ≥ III) within 6 months prior to inclusion.

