**Figure 2 Fig2:**
[figure not shown]
**IRE equipment.** The NanoKnife IRE console **(A)** utilizes 19G monopolar needle electrodes **(B)** which can be locked together using external spacers **(C)**.

The IRE procedure will take place at the Radiology department CT-room under general anaesthesia with muscle relaxation, as described by Nielsen et al. [25]. An interventional radiologist accompanied by a urological surgeon will perform the procedure. ECG monitoring and synchronization of IRE pulses will be performed under anaesthetic supervision. Needle electrodes (Figure 2B) will be placed under ultrasound and CT guidance using external spacers (Figure 2C) for fixation during pulse administration. Probe number and placement will be adjusted for specific tumour size or targeted tissue ablation in case of clinical tumor stage ≥ cT1b. Currently practiced IRE settings for tumour ablation are electrode spacing of 15 mm, electrode tip exposure of 15 mm, 90 pulses of 90 μs (synchronised with ECG) and a pulse intensity of 1500 V/cm. The IRE treatment cycle will take 5–10 minutes; total operating time is estimated at 90 minutes. If deemed clinically fit, patients will be discharged 24 hours after the IRE procedure. Post procedural pain will be quantified at 4 hours, 24 hours and 1 week by means of VAS score, cumulative opiate use and patient satisfaction.

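### The ASA exclusion in Table 1, as printed, bars categories I to IV and admits only patients above IV, which contradicts the population and procedures described elsewhere; its direction and its handling of category IV must be reconciled

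*Protocol article*

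**What the plan says.** The Population section of the protocol article sends the reader to one place for the eligibility rules: "The inclusion and exclusion criteria for this study are listed in Table 1". That section also gives some conditions in prose (age, and the reasons for which a patient is a candidate for radical nephrectomy), but no ASA limit.

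Table 1 has two columns. The exclusion column contains "Anaesthesia Surgical Assignment (ASA) cat. ≤ IV". ASA is mentioned nowhere else in the article. A footnote to the same table defines severe cardiovascular disease, another exclusion, and this definition includes "severe cardiac failure (NYHA class ≥ III) within 6 months prior to inclusion".

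The rest of the article describes the patients and what they undergo:

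- Population: "Ten patients with a solid enhancing renal mass and scheduled for a radical nephrectomy will be enrolled in this study".
- IRE ablation (study intervention): the procedure is done "under general anaesthesia with muscle relaxation, as described by" a cited report. Afterwards, "If deemed clinically fit, patients will be discharged 24 hours after the IRE procedure".
- Radical nephrectomy (standard treatment): open or laparoscopic surgery four weeks after IRE.
- Potential benefits and risks: participants gain no benefit and carry extra risk. "They will have to undergo an additional procedure under general anaesthesia with muscle relaxation".

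**The concern.** ASA category is the only anaesthetic-risk criterion in Table 1, and the study adds one general anaesthetic without benefit to the participant. A criterion of this kind would be expected to keep out patients at the high-risk end of the scale. The printed line does the opposite: it keeps out everyone up to and including category IV.

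Two things are at stake. First, a screener who follows Table 1 to the letter could not recruit the planned sample. Second, a screener who sees that the line cannot be meant literally has to guess the intended rule, and more than one guess is reasonable. Safety is a primary objective, so a reader of the results needs to know which risk categories the safety findings cover.

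**Working it through.** No error rate, power or sample-size figure is involved, and the plan gives no figure to reproduce. The check is set logic on an ordered scale, followed by a comparison of sections.

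**Assumption.** ASA categories run upward in risk from I to V, or to VI if the donor category is counted. The article does not define the scale.

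**Step 1: the rule as printed.**
- Excluded: categories ≤ IV = {I, II, III, IV}.
- Admitted: what remains = {V}, or {V, VI}.

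**Step 2: is the sign a reading artefact of the PDF?** This is unlikely. In Table 1 and its footnote the sign ≥ appears correctly for age (≥ 18 years) and for NYHA class (≥ III). It appears again for clinical stage (≥ cT1b) in the IRE ablation section. The sign ≤ appears with its proper meaning in the Discussion (tumours ≤ 4 cm). The two signs are distinguished throughout, and the ASA entry stands in the same column as the other exclusions.

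**Step 3: compare the admitted set with the rest of the article.**

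| Source | What it implies | Compatible with admitting only categories above IV? |
|---|---|---|
| Population; Table 1, inclusion column | Scheduled for open or laparoscopic radical nephrectomy | No |
| IRE ablation; Potential benefits and risks | An additional general anaesthetic with muscle relaxation | No |
| IRE ablation | Discharge planned at 24 hours if fit | No |
| Radical nephrectomy | Surgery four weeks later | No |
| Table 1 footnote | NYHA class III and above within 6 months excluded, so the sicker end is removed | Opposite direction |

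The incompatibility in the first four rows is an inference from the conventional meaning of the top of the scale. The last row can be read directly from the table. Taken together, they leave effectively no eligible patients against a planned sample of 10.

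**Step 4: what might have been meant?** Two simple drafting errors would each explain the line.
- Wrong sign: exclude ≥ IV. Admitted = {I, II, III}.
- Wrong column: include ≤ IV. Admitted = {I, II, III, IV}. An exclusion of > IV gives the same set.

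The two sets differ by exactly {IV}. Nothing in the article decides between them.

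**Step 5: size of the ambiguity.** With 10 patients, one category IV patient is 1/10 = 10% of the safety data and two are 2/10 = 20%. The article gives no ASA distribution, so the number of such patients to expect is unknown. Population does admit patients with stage 4 or 5 renal disease, and Potential benefits and risks says that patients with renal insufficiency have not yet been studied. Whether the upper end of the risk scale is eligible is therefore a practical question.

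**The case against.** The strongest reply is that this is an evident slip. Nobody chose to enrol only patients above category IV, and the literal rule is so implausible that it is unlikely to be applied. Population states that a nephrologist reviews every inclusion for safety and eligibility. The article describes the approval and practice of one centre. No endpoint or planned summary depends on the line, since the Sample size section confines results to averages and standard deviations of volumetric data.

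Most of this stands. The point is a drafting error and an internal contradiction, not a flawed design choice. But the nephrologist's review does not repair the text, because the reviewer also needs a stated rule. And recognising the slip settles the direction but not whether category IV is eligible.

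A reader might go further in three ways that the article does not support:

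- **Each investigator will set a personal threshold.** With one centre described and central review of each inclusion, such drift is not shown.
- **The safety result becomes undefined.** Adverse events are graded by CTCAE v4.0 in the treated patients, and that definition holds whatever the ASA limit. What is unclear is only to whom the result applies.
- **The cure is simply to reverse the inequality.** That presumes the wrong-sign explanation. The wrong-column explanation fits equally well and gives a different answer for category IV.

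It could also be argued that every other exclusion removes high-risk patients, so the intent is plain. That is too broad: previous ablation or partial nephrectomy of the affected kidney concerns prior treatment and is not evidently an anaesthetic risk. The NYHA footnote is the better evidence of intent.

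**Conclusion.** The point holds as a contradiction within the protocol article. On the conventional ASA ordering, the printed criterion excludes categories I to IV and admits only those above IV. This opposes the population and procedures described elsewhere and the direction of the table's own NYHA exclusion. That essentially no patient scheduled for elective radical nephrectomy would qualify is an inference from that ordering and the trial's setting; the article gives no ASA data from which to compute a proportion.

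The lasting consequence is narrower than an empty trial: the eligibility of category IV is ambiguous, and so is the population to which the primary safety result applies. No analysis, volume estimate or error rate is affected. Correction is still needed, because this is an operative, safety-related eligibility rule that is wrong as written and that no other section corrects.

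**What to change.** - Reconcile the ASA line in Table 1 with Population, IRE ablation, Radical nephrectomy, and Potential benefits and risks.
- Restate it so that both its direction and its handling of category IV are unambiguous, in the form that stands in the IRB-approved protocol. The cut-off is for the sponsor and the IRB to confirm; this review does not propose one.
- Check the screening log to see that patients already screened were judged against that rule, and record any who were not.

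The cost is a one-line erratum and a log check for a study of ten patients. Sample size, endpoints and planned summaries do not change.
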